### Types of outcomes

#### Efficacy outcomes

The primary outcome is END on the third day of onset defined as an increase of 2 or more points in the NIHISS score between baseline and day 3. The secondary outcomes include the rates of stroke-related and any-cause deaths during hospitalization, differences in the changes in the neurological deficit degree, risk grade of ICH evaluated through changes in the ICH scale score from baseline to day 10 or the day of discharge, the proportion of patients with activities of daily living with a Barthel Index score of ≥90, and the proportion of independent patients defined by a modified Rankin Scale score ≤2 at 30 ± 3, 60 ± 3, and 90 ± 7 days after stroke onset. A complete list of the efficacy outcomes analyzed in the TRACE study is presented in Table 2.

**TABLE 2 T2:** | The complete list of efficacy outcomes analyzed in the TRACE study.

Primary outcome
1. Early neurological deterioration# change
Early neurologic deterioration (END) is defined as an increase of 2 points or more in the National Institute of Health Stroke Scale (NIHSS) score between baseline and 3 days. The NIHSS score ranges from 0 (best score) to 42 (worst score). [Time Frame: between baseline and 3 days]
Secondary outcomes
1. Rate of stroke-related deaths and deaths from any cause Rate of stroke-related deaths and deaths from any cause during hospitalization [Time Frame: during hospitalization] 2. Neurological deficit Comparison of the change of degree of neurological deficit evaluated by the NIHSS [Time Frame: baseline and day 10 or the day of discharge] 4. Risk grade of a cerebral hemorrhage Comparison of the change of risk grade of Intracranial hemorrhage evaluated by Intracerebral Haemorrhage (ICH) scale. The ICH score ranges from 0 (best score) to 6 (worst score). [Time Frame: baseline and day 10 or the day of discharge] 5. Activities of daily living Activities of daily living will be measured by Barthel Index (BI) score. The proportion of patients with a BI score of ≥ 90. The BI score ranges from 0 (worst score) to 100 (best score). [Time Frame: 30, 60, and 90 days] 6. The proportion of patients’ independent The proportion of patients’ independence is defined as a modified Rankin Scale (mRS) score of ≤ 2. The mRS score ranges from 0 (best score) to 6 (worst score). [Time Frame: 30, 60, and 90 days]

Note: Baseline score refers to the NIHISS and ICH scores within 24 h of symptom onset (assessed in a prehospital ambulance or after admission). Abbreviations: TRACE, Trial of a prehospital intervention with traditional Chinese medicine for acute stroke; NIHSS, National Institutes of Health Stroke Scale; ICH, intracerebral hemorrhage; BI, Barthel Index; mRS, modified Rankin Scale.

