### Recruitment

Patients will be recruited consecutively from 20 participating sites, including both Western medicine hospitals and TCM hospitals in Beijing, China, which have the capability of conducting qualified research and express a proven commitment to the study. The recruitment started in March 2018 and is estimated to end in December 2022. Eligible adult patients with suspected acute stroke within 24 h of onset will be sent to the hospital by ambulance. We plan to recruit 1,000 patients with confirmed acute stroke based on the inclusion and rejection criteria. The time of stroke onset was defined as the time at which the patient was last observed to be well. Only those who meet the inclusion criteria and willingly provide written informed consent will be recruited. Since this is an observational study that involves a specific prehospital emergency intervention, it is difficult to obtain written informed consent from the patient in the prehospital ambulance setting. The patient will be asked to sign a written informed consent form in the hospital. The researchers will inform patients of the benefits and risks of participating in the research and of the need to analyze their prehospital information in addition to their in-hospital information; they will also be assured that this will not interfere with the actual clinical diagnosis and treatment. Legal guardians will sign the informed consent form on behalf of patients in a coma. If the patient or his legal guardian does not agree to the use of the diagnosis and treatment-related information in this study, the prehospital information will not be used. The participation of patients will be entirely voluntary, and their data will be strictly protected to the extent permitted by the law.

In this study, to increase the rate of identifying suspected stroke patients, the prehospital assessment scale for identifying these patients was changed from the Face-Arms-Speech-Time (FAST) scale to the Balance-Eyes-Face-Arms-Speech-Time (BEFAST) scale. Once meeting the inclusion criteria, patients will be included and registered immediately in an ambulance. However, due to the busy task and high tension in the prehospital ambulance setting, ambulance doctors are unable to exclude patients in detail. The ineligible patients will be rejected after admission. Therefore, this study has changed the exclusion criterion to the rejection criterion. 

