TOAST classification of AIS	Major artery Atherosclerotic stroke; Cardiogenic cerebral embolism; Arterial occlusive stroke or lacunar stroke; Ischemic stroke resulting from other causes; Unknown cause of ischemic stroke
Major treatment methods	IVT and EVT for AIS; Surgery (craniotomy hematoma removal; minimally invasive surgery; bone valve decompression; ventricular drainage) and others for ICH
In-hospital medication	Antihypertensive agents; Hypoglycemic agents; Lipid-lowering drugs; Anticoagulants; Hemostatic agents; Reduced cranial pressure agents; Anticoagulants agents; XNJI (start use time; stop use time; use frequency; administration duration time; dose); Other TCM (Chinese patent medicine injection agent; Chinese patent medicine oral agent; TCM soup agent)
In-hospital rehabilitation	Acupuncture and moxibustion; Massage; PT; OT; ST; Others
Auxiliary examination	Vital signs; Laboratory tests; Cranial CT or MRI; ECG
Complication	Lung infections; Urinary tract infections; Upper gastrointestinal bleeding; Hiccups; Dysphagia; Urine retention; Urinary incontinence; Pressure ulcers; Kidney failure; Pulmonary embolism; Epilepsy; Shoulder-hand syndrome; Post-stroke depression; Post-stroke anxiety; Others
Indicators on health economics	Hospitalization costs; Treatment costs; Inspection fees; Medicine costs; Other costs; Total costs; Number of days of hospitalization
Discharge diagnosis	
In-hospital mortality	
Discharge evaluation	NIHSS; ICH Scale and GCS for ICH
Visit 5 (day 30 ± 3 after symptom onset)	
Follow-up evaluation	mRS; BI
Visit 6 (day 60 ± 3 after symptom onset)	
Follow-up evaluation	mRS; BI
Visit 7 (day 90 ± 7 after symptom onset)	
Basic medication	Antithrombotics agents; Anticoagulants agents; Lipid-lowering drugs; Antihypertensive agents; Hypoglycemic agents; TCM
Rehabilitation	Acupuncture and moxibustion; Rehabilitation exercise
Follow-up evaluation	mRS; BI
AEs (during the observation period)	Start time; Symptoms/signs; Intensity; Attack frequency; Duration and termination time; Laboratory indicators; Treatment methods and outcomes; Follow-up results

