### Data processing and analysis

The mean (Mean), standard mean difference (SD), median (Median), interquartile ranges, minimum (Min), and maximum (Max) will be used to summarize continuous data, while rate or percentage will be used for categorical data. Between-group comparisons will be conducted using parametric or non-parametric tests, as appropriate. Pearson’s chi-squared test is used for the count data, and the results are expressed as rate or percentage (%). Measured data, if data are normally distributed and the variance is homogeneous, the parametric test (*t*-test) will be used and results will be expressed as mean ± SD; If the data are not normally distributed and still do not meet the requirements for the parametric test after data conversion, the non-parametric test (Wilcoxon rank sum test or Mann-Whitney U test) will be used and results will be expressed as median (Median).

As the primary analysis, a comparison of the presence of END on the third day after stroke onset will be conducted between the two groups of patients—the exposure group and the nonexposure group—using Pearson’s chi-squared test. The secondary outcome analyses will involve the rate of stroke-related and any-cause deaths, differences in the NIHISS scores, differences in the ICH scale scores, proportion of patients with BI scores ≥90, and proportion of patients with mRS scores ≤2. These analyses will be performed according to the standard statistical principles for comparing parametric or non-parametric distributions, as appropriate. During the analysis, multivariate linear regression analysis is performed for the influencing factors that are statistically significant in the univariate analysis. The full analysis set will be used in the efficacy correlation analysis in this study. The safety analysis set will be used in the safety analysis. The full analysis set refers to the set of eligible cases and detached cases but not eliminated cases. The safety analysis set will consist of safety indicators for all enrolled subjects with post-medication safety evaluation data; the number of subjects with missing data will be reported. All statistical tests will be one-sided, and statistical significance will be set at *p* < 0.05. SAS software, version 9.2 (SAS Institute, Inc., Cary, NC, United States), will be used to perform the statistical analyses.

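### The primary outcome, END, rests only on a day-3 NIHSS increase and gives no status to patients who die first, so unequal early mortality would distort the comparison in either direction

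*Protocol article*

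**What the plan says.** The Efficacy outcomes section defines the primary outcome as "END on the third day of onset defined as an increase of 2 or more points in the NIHISS score between baseline and day 3". Table 2 repeats that this outcome "is defined as an increase of 2 points or more in the National Institute of Health Stroke Scale (NIHSS) score between baseline and 3 days", and the Abstract gives the same rule. The NIHSS is described as running from 0 to 42, with no value for death.

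Death enters the efficacy outcomes separately, as a secondary outcome: "the rates of stroke-related and any-cause deaths during hospitalization". In Table 1, survival or death is listed at Visits 1 and 2, and "In-hospital mortality" at Visit 4.

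Under Data processing and analysis, the primary analysis is a Pearson chi-squared test: "a comparison of the presence of END on the third day after stroke onset will be conducted between the two groups of patients". All tests are one-sided at 0.05. On the analysis population: "The full analysis set refers to the set of eligible cases and detached cases but not eliminated cases". That fixes who belongs to the set, but not the END status of a member without a day-3 score.

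The Recruitment section shows that very severe strokes are enrolled: "Legal guardians will sign the informed consent form on behalf of patients in a coma". Both ischaemic stroke and ICH are included, and the rejection criteria do not mention coma or severity.

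**The concern.** A patient who dies on day 1 or 2 has had the worst possible deterioration but has no day-3 NIHSS, so cannot meet the definition as written. Two literal readings remain. Leaving such patients out restricts the comparison to those who survive to day 3, which is a selection made after exposure. Counting them as non-END puts deaths among the good results.

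Under either reading the primary comparison depends on how early deaths divide between the groups. Clinicians decide treatment, so nothing in the design makes early mortality equal. Adjusting for baseline factors would not settle how the deaths are classified. What is at stake is a primary result that could be favourable because of deaths, or that could hide a real benefit if XNJI patients die less often.

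The secondary proportion with a Barthel Index of at least 90 has the same gap: no rule places deaths in its denominator.

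**Working it through.** **Inputs.** From the protocol article: one-sided test at 0.05; 1,000 patients; planning END rates of 13% (nonexposed) and 7% (exposed). The article gives no death rate by day 3, so there is no figure of its own to reproduce here. Assumed: 500 per group; early death proportions as shown; and, in the main illustration, the same 11% of patients in each group with END or death by day 3, so that there is no true benefit.

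**Step 1. END among survivors, if deaths are left out.** With d the proportion dying before day 3, END among survivors = (0.11 − d)/(1 − d).
- d = 0.02: 0.09/0.98 = 9.2% (45 of 490)
- d = 0.03: 0.08/0.97 = 8.2% (40 of 485)
- d = 0.04: 0.07/0.96 = 7.3% (35 of 480)
- d = 0.05: 0.06/0.95 = 6.3% (30 of 475)

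**Step 2. The planned test at 5% versus 2% early deaths.** Pooled proportion = (30 + 45)/(475 + 490) = 0.0777. Standard error = √[0.0777 × 0.9223 × (1/475 + 1/490)] = 0.0172. z = (0.0918 − 0.0632)/0.0172 ≈ 1.66, just above the critical value of 1.645. The chance of declaring a benefit is about 51%.

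**Step 3. Chance of a false one-sided benefit.**

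| Early deaths, exposed vs nonexposed | Deaths left out | Deaths counted as non-END | Deaths counted as events |
|---|---|---|---|
| 2% vs 2% | 5% | 5% | 5% |
| 3% vs 2% | 13% | 14% | 5% |
| 4% vs 2% | 28% | 32% | 5% |
| 5% vs 2% | 51% | 56% | 5% |

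With END or death at 13% instead of 11% in both groups, 5% versus 2% gives 43% (left out) or 49% (non-END).

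**Step 4. Opposite direction.** With 2% deaths in the exposed and 5% in the nonexposed, the Step 1 rates swap to 9.2% versus 6.3%, z ≈ −1.66. The chance of declaring a benefit falls below 0.1%: the distortion now runs against XNJI.

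**Step 5. A different construction.** Suppose END among survivors is equal, say 9.2% in both groups, with deaths of 5% versus 2%. If deaths are left out, the chance of a declared benefit stays at 5%. The combined rate is then 0.05 + 0.95 × 0.0918 = 13.7% against 0.02 + 0.98 × 0.0918 = 11.0%, an excess of bad outcomes that the primary comparison does not register.

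**Step 6. Scale.** The planning rates imply 0.07 × 1,000 = 70 to 0.13 × 1,000 = 130 END events. If 1% to 5% of patients died before day 3 (assumed), that is 10 to 50 patients, which is not small beside 70 to 130.

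**The case against.** The strongest reply is that the article states no wrong rule, only none. Handling of absent assessments is commonly left to the analysis plan, which is not shown and could count deaths as END. This holds for ordinary missing scores. It holds less well for death: the article states the primary outcome in full, three times, and whether the most severe deterioration is an event belongs to that definition. A dead patient has no NIHSS to impute.

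Other objections stand and limit the point:
- A reader might infer that early deaths are dropped. No section says so, and the full analysis set as described does not remove them. Exclusion is one literal reading; counting as non-END is the other.
- A reader might also infer that the bias favours a harmful treatment. That requires more early deaths among the exposed, and the documents report no early mortality.
- The 13%, 28% and 51% depend on holding END or death at 11% in both groups, so that each excess death replaces an END case. Step 5 shows that another construction gives no inflation when deaths are left out.
- The 500/500 split is assumed, and the article itself expects uneven exposure. Consent is signed in hospital, so some very early deaths may never be enrolled.
- Deaths are not hidden: in-hospital death is a listed secondary outcome. It would show an excess but would not correct the primary comparison.
- The mRS outcome needs no repair, because its stated 0 to 6 range already makes death a failure of mRS ≤2.

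**Conclusion.** The point holds as a gap in the definition of the primary outcome. No END status is given to patients who die before the day-3 assessment, and both literal readings make the result depend on the balance of early deaths between non-randomised groups. The direction is conditional: towards XNJI if exposed patients die early more often, against it if less often, and no false benefit if the rates are equal.

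The size cannot be fixed from the documents. Under the stated assumptions, an excess of 1 to 3 percentage points in early deaths raises the false-benefit rate from 5% to between 13% and 51%, or to 14% to 56% if deaths are coded non-END. The documents do not support saying that XNJI increases early death, or that a false benefit is likely. This should be corrected before analysis.

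**What to change.** Before data lock, and by a documented amendment:
- Define the primary outcome as an NIHSS increase of at least 2 points from baseline to day 3, or death from any cause before the day-3 assessment.
- Record the date of death, so that deaths by day 3 can be identified, and report them by group.
- Keep NIHSS-only END as a sensitivity analysis.
- Count deaths as not reaching a Barthel Index of 90. Leave the mRS outcome as it is.

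Collection costs little, since in-hospital mortality is already recorded. The real costs are three. The outcome becomes a composite. Its event rate rises slightly, while the 13% and 7% planning rates refer to NIHSS-only END, so the sample-size basis no longer matches exactly. And the change is late: recruitment was due to end in December 2022 and the article appeared in August 2022, so the amendment must carry its date and reason and state that it preceded any comparison of outcomes by group.

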### Inclusion criteria

•Diagnosis of suspected acute stroke•Within 24 h of symptom onset•Age≥18 years

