### Rejection criteria

•Other diseases that lead to motor dysfunction (e.g., claudication, severe osteoarthritis, rheumatoid arthritis, and gouty arthritis)•Other diseases or psychosis that renders outcome assessments or follow-up unlikely to be possible•Known to be pregnant or lactating•Non-acute stroke [result from Computed Tomography (CT) or Magnetic Resonance Imaging (MRI)].

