### Intervention measures

The quantitative research part of this study will be observational. Based on our observation of whether XNJI was intravenously administered within 24 h of onset in the prehospital ambulance setting, patients with acute stroke will be divided into two groups: the exposure group comprising patients who were intravenously administered XNJI and the nonexposure group comprising patients who were not. During the study period, all relevant data will be collected at the following timepoints to facilitate a continuous dynamic observation and evaluation: during the prehospital ambulance service; within 24 h of admission; day 3 after stroke onset; day 10 after stroke onset or the day of discharge; and 30 ± 3, 60 ± 3, and 90 ± 7 days after stroke onset. This research will not interfere with the actual diagnosis and treatment of the participants. The clinicians will make decisions regarding routine treatment options based on the patient’s specific circumstances. The routine stroke treatment will follow the current national guidelines for acute Is and ICH from the Chinese Society of Neurology.

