### Main variables

All variables used for outcomes evaluation of efficacy and safety are abstracted from all relevant data collected during the observation period. The main variables of this study are listed in Table 1.

**TABLE 1 T1:** Main variables registered in the TRACE study.

Field	Variables
Visit 1 (during pre-hospital ambulance service)	
Demographics information	Name; Age; Gender; ID number
Condition, state of consciousness, and survival or death upon ambulance arrival	Time of symptom onset; Time of ambulance arrival; State of consciousness; Survival/death; Stroke assessment (BEFAST)
Usage of XNJI	Use it or not; Time of first use of XNJI; Dose
Concomitant medication	Antihypertensive drugs; Vasopressor drugs; Hypoglycemic agent; Glycemic drugs; Other drugs
Auxiliary examination	Vital signs
Indicators on health economics	Treatment costs; Inspection fees; Medicine costs; Other costs; Total costs
Prehospital evaluation	NIHSS
Visit 2 (within 24 h after admission)	
Condition, state of consciousness, and survival or death upon arrival	Time of onset, Time of arriving at the hospital; State of consciousness; Survival/death
Baseline information	Height; Weight; BMI; Being overweight or obese; Predisposing factors; Transient symptoms occurred within 2 months before stroke onset; Past medical history (strokes; CHD; atrial fibrillation; diabetes; hypertension; hyperlipidemia; apnea); Personal history (smoking; alcohol consumption); Family history; Drug allergy history; Treatment history within 2 weeks before admission
Auxiliary examination	Vital signs; Laboratory tests; Cranial CT or MRI; ECG
Complication	Lung infections; Urinary tract infections; Upper gastrointestinal bleeding; Hiccups; Dysphagia; Urine retention; Urinary incontinence; Pressure ulcers; Kidney failure; Pulmonary embolism; Epilepsy; Shoulder-hand syndrome; Post-stroke depression; Post-stroke anxiety; Others
Admission evaluation	mRS; NIHSS; ICH Scale and GCS for ICH
Visit 3 (day 3 after symptom onset)	
Auxiliary examination	Vital signs
Complications	Lung infections; Urinary tract infections; Upper gastrointestinal bleeding; Hiccups; Dysphagia; Urine retention; Urinary incontinence; Pressure ulcers; Kidney failure; Pulmonary embolism; Epilepsy; Shoulder-hand syndrome; Post-stroke depression; Post-stroke anxiety; Others
In-hospital evaluation	NIHSS; ICH Scale and GCS for ICH
Visit 4 (day 10 after symptom onset or the day of discharge)	

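### mRS ≤2 and BI ≥90 are compared between non-randomised groups with no pre-stroke function among the listed variables, so an imbalance in prior dependence would bias these secondary outcomes in either direction

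*Protocol article*

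**What the plan says.** Under Efficacy outcomes, two secondary outcomes are fixed cut-offs on follow-up scales at 30, 60 and 90 days: "the proportion of independent patients defined by a modified Rankin Scale score ≤2", and, in Table 2, "The proportion of patients with a BI score of ≥ 90". Neither refers to function before the stroke.

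Entry is broad. The inclusion criteria are "Diagnosis of suspected acute stroke•Within 24 h of symptom onset•Age≥18 years", so neither a first-ever stroke nor a minimum level of prior function is required. One rejection criterion touches prior disability: "Other diseases that lead to motor dysfunction (e.g., claudication, severe osteoarthritis, rheumatoid arthritis, and gouty arthritis". A second removes patients whose other diseases or psychosis make assessment or follow-up unlikely to be possible.

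Table 1 lists earlier strokes as history only: "Past medical history (strokes; CHD; atrial fibrillation; diabetes; hypertension; hyperlipidemia; apnea". The Visit 2 admission evaluation is "mRS; NIHSS; ICH Scale and GCS for ICH", made within 24 h after admission. BI first appears at day 30. The note to Table 2 says "Baseline score refers to the NIHISS and ICH scores within 24 h of symptom onset"; it defines no baseline for mRS or BI.

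On allocation, the Intervention measures section states "The quantitative research part of this study will be observational". Under Data processing and analysis, secondary outcomes receive standard group comparisons, regression is limited to factors that were significant in univariate analysis, and all tests are one-sided at 0.05.

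**The concern.** A patient who already had an mRS of 3 to 5 before this stroke can be counted at mRS ≤2 only by ending better than before it. Such patients fall almost entirely on one side of the threshold, whatever treatment they receive in the ambulance.

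In a randomised trial this would mainly cost precision, because prior dependence would balance in expectation. Here clinicians decide who receives XNJI. Prior dependence could plausibly influence that decision, and it strongly determines both outcomes. If its share differs between groups, the difference passes into the mRS and BI comparisons at all three time points. A factor that is not recorded cannot enter the planned regression.

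**Working it through.** **1. Is there a listed measure of prior function?** Going through Table 1 visit by visit:

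- Visit 1 has NIHSS and BEFAST, both rating the acute state.
- Visit 2 has mRS, NIHSS and, for ICH, the ICH scale and GCS, all after onset. It also has history items, which include earlier strokes but not what those strokes left behind.
- Visits 3 and 4 have NIHSS, ICH scale and GCS.
- Visits 5 to 7 have mRS and BI at follow-up.

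No item is labelled as pre-stroke function. The telephone form described under Follow-up procedures adds only medication and rehabilitation.

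**2. Do the rejection criteria close the gap?** In part. The motor-dysfunction criterion names claudication and joint diseases as examples. It refers to other diseases and does not say whether the sequelae of an earlier stroke count. The criterion on non-acute stroke concerns what imaging shows of the current event, so it does not remove a new stroke on top of an old one.

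**3. How large could the bias be?** The article gives no share of previously dependent patients and no expected mRS or BI proportion, so there is no figure of its own to reproduce. Inputs:

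- s0, the proportion of previously independent patients who reach the threshold: assumed 0.50 to 0.70.
- Proportion of previously dependent patients who reach it: assumed 0.
- Drug effect: assumed none.
- a and b, the shares previously dependent among exposed and nonexposed patients: assumed.
- 500 per group: the planned 1,000 split equally (an assumption; the article itself expects uneven exposure).
- One-sided test at 0.05 (article), taken in the direction favouring XNJI (assumption).

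Expected proportions are s0(1 − a) and s0(1 − b), so the spurious difference is s0(b − a). For s0 = 0.60, a = 5% and b = 10%: 0.60 × 0.95 = 57.0%, 0.60 × 0.90 = 54.0%, difference 3.0 points.

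| Dependent, exposed vs nonexposed | Spurious difference, s0 = 0.50 / 0.60 / 0.70 | Chance of a one-sided significant result |
|---|---|---|
| 10% vs 10% | 0 / 0 / 0 points | 5% / 5% / 5% |
| 5% vs 10% | 2.5 / 3.0 / 3.5 points | 20% / 25% / 31% |
| 5% vs 15% | 5 / 6 / 7 points | 48% / 60% / 74% |
| 10% vs 20% | 5 / 6 / 7 points | 48% / 60% / 73% |

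Example for the last column, 57% vs 54%: the pooled proportion is 0.555, the standard error is √(2 × 0.555 × 0.445 / 500) = 0.0314, and 0.03 / 0.0314 = 0.95. The chance of exceeding 1.645 is Φ(0.95 − 1.645), about 25%.

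**4. Sensitivity.** If a proportion d0 of previously dependent patients does reach the threshold, the difference becomes (s0 − d0)(b − a), so the table shows the upper end for each imbalance. The same formula holds for BI ≥90 with that scale's own s0 and d0. Swapping a and b reverses the sign, and the bias then works against XNJI.

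**The case against.** **The article is condensed.** Table 1 is introduced as the main variables and the full case report form is not shown. This stands: one can say that no such item is listed, not that none is collected. The table is nevertheless detailed enough to itemise hiccups and apnea, and the outcome definitions would ignore a pre-stroke item even if one existed.

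**The admission mRS might be a pre-stroke rating.** The article does not say which state it rates. A scale listed beside NIHSS and GCS in an admission evaluation most naturally describes the current state, and nothing labels it otherwise.

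**There is partial protection.** Both rejection criteria could remove some dependent patients, and age, earlier strokes and NIHSS are recorded. This also stands. A reader might infer that nothing in the data could separate prior dependence from an XNJI effect; that goes too far. Adjustment for these proxies would help, though incompletely: a history of stroke does not distinguish full recovery from lasting dependence.

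**The outcome is called independence, not success.** A patient who was dependent before and remains so is correctly described as not independent. A reader might infer that the plan scores such patients as treatment failures, but the article uses no such label. The problem lies in the comparison between non-randomised groups, not in the description of a patient.

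**General limitations are declared.** The Discussion concedes that the pre-designed form may lose key information and calls the evidence preliminary. It does not mention prior function.

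**Conclusion.** The gap is real but limited. Two secondary outcomes, each at three time points, use absolute thresholds without a listed measure of prior function, in a study where exposure is not randomised. On the stated assumptions, each 5-point imbalance in prior dependence moves the comparison by about 2.5 to 3.5 points.

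A reader might go further and conclude that these outcomes will favour XNJI. The documents do not support that: they give neither the size nor the direction of any imbalance, and equal shares produce no between-group bias, only lower proportions in both groups. The point does not extend to the primary outcome either, since END is a change in NIHSS from baseline to day 3 and a stable earlier deficit largely cancels.

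**What to change.** - Add pre-stroke mRS as a separate Visit 2 field, taken from the admission record, or from a remaining scheduled call where one exists.
- Adjust or stratify the mRS ≤2 and BI ≥90 comparisons by it, whether or not it passes univariate screening. Add a sensitivity analysis restricted to pre-stroke mRS ≤2.
- Where it cannot be recovered, pre-specify adjustment for the already recorded prior stroke, age and baseline NIHSS, and state the residual confounding as a limitation.
- Do not use the acute admission mRS as the pre-stroke baseline.

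The cost is one field, record abstraction and a modest change to the analysis. Scheduled calls will help few patients: recruitment began in March 2018 with an estimated end in December 2022, and the article appeared on 29 August 2022. Anyone with onset more than 97 days before that date (90 + 7), that is before about 24 May 2022, had passed the last call. That is roughly 51 of the 58 planned recruitment months. Some values for patients already enrolled will therefore be missing or recalled after the outcome is known, which is why the restricted analysis is better kept as a sensitivity analysis.
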